A maximum of a 14-day (21-day in consultation with the CI) delay in dosing for cediranib is permitted. If a longer interruption is required due to unresolved toxicity, cediranib should be discontinued. In addition, there are certain circumstances in which study medication should be permanently discontinued (see [section 13.1](#)).

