| Severe hypertension:

Increase in diastolic pressure to $\geq 110$ mmHg or increase in systolic pressure to $\geq 180$ mmHg on 2 readings >1 hour apart | 
 
1. Temporarily stop cediranib and consider if hospitalisation is necessary.
 
2. Initiate treatment with a 2-drug combination including a calcium channel blocker licensed for use in severe hypertension, tailored to the patient's underlying conditions and previous anti-hypertension treatment.
 
3. If there is evidence of target-organ damage, intravenous therapy should be considered while continuing oral therapy.
 
4. Nitrates may adversely affect the therapeutic mechanism of action of cediranib but should be used if clinically indicated.
 
5. Restart cediranib at 1 dose lower than the starting dose when BP <140/90 mmHg. Monitor BP every 3 to 7 days until steady state is BP stabilised
 
6. If BP increases to >160/95 mmHg, temporarily stop cediranib and continue anti-hypertensive therapy under close supervision.
 
7. Restart cediranib at 2 doses lower than the starting dose when BP <140/90 mmHg. Monitor BP every week until steady state is BP stabilised.
 
8. If BP increases to >160/95 mmHg after dose reduction to 15 mg od, despite anti-hypertensive therapy, permanently stop cediranib.
 
 |

The development of hypertension in patients treated with cediranib is generally an early event, usually occurring in the first 4 weeks of treatment. In a minority of patients hypertension can also occur later in a treatment schedule.

The rigorous monitoring of BP and adherence to the hypertension management guidelines are necessary in order to achieve optimal hypertension control. Patients on prior anti-hypertension therapy may be particularly at risk of developing moderate or severe hypertension on cediranib. Therefore, patients with pre-existing hypertension or on anti-hypertension medications are likely to benefit from having their BP management optimised before starting cediranib.

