#### 13.1.1 Discontinuation of Trial Drugs

In addition, both trial drugs should be permanently discontinued in patients with the following conditions:

- Gastrointestinal perforation or wound dehiscence requiring medical intervention
- Serious haemorrhage, i.e., requiring medical intervention
- Severe hypertension (see [section 7.4.1.4](#) for hypertension management protocol)
- Nephrotic syndrome
- Severe arterial thromboembolic event
- If any case of RPLS occurs that is confirmed by imaging (CT or MRI), trial drugs should be immediately discontinued, in addition to any other measures to alleviate symptoms and control blood pressure
- Patients should not receive trial drugs within 2 weeks of major surgery. Where possible, trial drugs should be suspended for 2 weeks to allow clearance before major surgery.
- Interstitial lung disease (ILD)
- Severe change in liver function

In these cases patients should continue to have trial assessments for the purposes of follow-up. If a patient wishes to withdraw from trial treatment, sites should explain the importance of remaining on trial follow-up, or failing this of allowing routine follow-up data to be used for trial purposes and for allowing existing collected data to be used.

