### 13.1.2 Procedures for discontinuation from treatment

Patients who discontinue the trial treatment should always be asked about the reason(s) for their discontinuation and the presence of any adverse events. If possible, they should be seen and assessed by an investigator(s). The patient should return investigational products.

If all study treatment is stopped during the study, the Principal Investigator/Sub investigator will perform the best possible observation(s), test(s) and evaluation(s) as well as give appropriate treatment and all possible measures for the safety of the patient. In addition, they will record on the Case Report Form (CRF) the date of withdrawal, the reasons, and treatment at the time of withdrawal.

If only one study treatment is stopped during the study, the patient will continue with the trial assessments as before. Reasons for stopping the first drug must be recorded on the CRF. The discontinuation assessment is only to be carried out upon discontinuation of both trial drugs.

At withdrawal, all on-going SAEs must be followed until resolution, unless in the Investigator's opinion, the condition is unlikely to resolve due the patient's underlying disease.

All new AEs occurring for up to 30 days after the last dose of any study medication must be recorded in the CRF. Ongoing AEs thought to be caused by trial treatment will be followed up until resolution or death. All SAEs occurring up to 30 days after the last dose of any study medication must be followed until resolution.

Patients who are not receiving treatment, but are being followed up for tumour assessments should also be followed up for procedure related SAEs, these should be reported on an SAE report form (see [section 10.2.2](#) SAEs). AE collection beyond the 30 days post treatment is not required for patients who have progressed and are being followed up for survival only.

For patients who are withdrawn from study treatment for reasons other than disease progression every effort will be made to continue with collecting the trial MRI scans every 6 weeks. Follow up clinic assessments should be carried out every 6 weeks as detailed in [section 8](#).

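### For severe hypertension, 13.1.1 permanently stops both trial drugs, but Table 7, to which it refers, restarts cediranib at lower doses and never says whether gefitinib/placebo stops

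*Protocol*

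**What the plan says.** Section 13.1.1 opens with a rule for both agents: "both trial drugs should be permanently discontinued in patients with the following conditions". Severe hypertension is one of the listed conditions. Its bullet carries only a pointer to section 7.4.1.4 "for hypertension management protocol".

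Table 7 in section 7.4.1.4 has a row with the same label, defined as diastolic pressure of at least 110 mmHg or systolic of at least 180 mmHg on two readings more than an hour apart. Step 1 of that row is "Temporarily stop cediranib and consider if hospitalisation is necessary". Step 5 is "Restart cediranib at 1 dose lower than the starting dose when BP" falls below 140/90 mmHg. If pressure then rises above 160/95 mmHg, step 6 is a second temporary stop and step 7 a restart two levels below the starting dose. Step 8 is the only permanent stop. It applies if pressure exceeds 160/95 mmHg "after dose reduction to 15 mg od, despite anti-hypertensive therapy, permanently stop cediranib". Mild-to-moderate step 13 ends in the same way.

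Section 7.4.1, which governs cediranib toxicity, says that "there are certain circumstances in which study medication should be permanently discontinued" and refers to 13.1.

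On procedures, section 13.1.2 states: "If only one study treatment is stopped during the study, the patient will continue with the trial assessments as before". It adds: "The discontinuation assessment is only to be carried out upon discontinuation of both trial drugs".

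**The concern.** Two sections give different instructions for an event with the same name. Read alone, 13.1.1 ends all trial treatment. Read alone, Table 7 interrupts one drug, reintroduces it at a lower dose, and leaves the other drug unmentioned. Each section refers to the other, and neither says which prevails.

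The event is foreseeable. Both arms start cediranib at 30 mg. Section 2.4.3.1 reports that hypertension at 45 mg was the main reason the maximum tolerated dose was set at 30 mg in combination with 250 mg gefitinib, although 45 mg was tolerated with 500 mg.

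Two investigators following the protocol in good faith could treat the same patient differently. One could stop both drugs. The other could re-expose the patient to cediranib and continue gefitinib/placebo. A statistical analysis plan would not settle this, because it is an instruction for the treating clinician.

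**Working it through.** No statistical figure is involved, so the check sets the provisions side by side.

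**Dose levels.** Table 5 gives cediranib 30 mg as level 0, 20 mg as level -1 and 15 mg as level -2. One and two levels below the starting dose are therefore 20 mg (step 5) and 15 mg (step 7). Step 8 itself names 15 mg, so the table is internally consistent on this.

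| Question | 13.1.1 | Table 7, severe row |
|---|---|---|
| Is the stop permanent? | Yes, by the list header | Temporary at steps 1 and 6; permanent only at step 8 |
| Is a restart allowed? | None mentioned | 20 mg at step 5, 15 mg at step 7 |
| Which drug stops? | Both | Only cediranib is named |

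**What Table 7 covers.** Steps 1, 5, 6, 7 and 8 stop or restart cediranib: 5 of 8. Steps that act on gefitinib/placebo: 0 of 8. Across the whole table, 13 + 8 = 21 steps, gefitinib is named in none. Mild-to-moderate steps 1 and 2 only say that all study medication continues unchanged.

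**Does the cross-reference settle it?** Two questions need separate answers.

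1. *When does treatment stop for good?* The pointer to 7.4.1.4 can reasonably be taken to mean that 13.1.1 applies once Table 7 reaches its permanent stop. That would remove the conflict over timing, but the bullet does not say it.
2. *Which drugs stop at that point?* Even on that reading, step 8 names cediranib and 13.1.1 names both. A site cannot assume that stopping cediranib stops everything, because continuing on one drug is an established option here. Note k in section 8.2 tells sites to continue the other drug when one is delayed too long for toxicity, and 13.1.2 sets procedures for that case.

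**What changes with the answer.**

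- Both drugs stopped: the discontinuation assessment is triggered (13.1.2). A patient who has not progressed moves from the on-treatment schedule (3-weekly after week 6) to 6-weekly follow-up (8.1; note h in 8.2). New adverse events are collected for 30 days after the last dose (note g), and the schedule shows no quality-of-life questionnaire in long-term follow-up.
- Only cediranib stopped: on-treatment visits continue and no discontinuation assessment is made.

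**What does not change.** MRI continues every 6 weeks after withdrawal for reasons other than progression (note f in 8.2; 13.1.2). PFS in 2.6.1.1 and the ITT population in 16.2 do not depend on treatment status.

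**The case against.** The strongest defence is that the two sections are meant to be read together. Severe hypertension is the only bullet in 13.1.1 that refers to a stepwise management plan, and 7.4.1 takes hypertension out of its general cediranib rules and sends it to 7.4.1.4. Where the authors wanted an instant stop, as for reversible posterior leukoencephalopathy syndrome (RPLS), they wrote it into the bullet. The list header is not literal for every entry either, since the major-surgery bullet describes a 2-week suspension. Table 7 sits under cediranib toxicity, so naming only cediranib is expected. There is also a pattern: 7.4.1.7 stops cediranib for RPLS and 7.4.2.2 stops gefitinib for interstitial lung disease, and 13.1.1 extends each to both drugs.

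Much of this stands. It makes Table 7 the likely authority on timing, and a both-drugs stop at step 8 the likely intent. But both have to be inferred. The pointer is bare, and note k in 8.2 with 13.1.2 supports the opposite inference about the second drug.

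The defence does rule out several stronger readings that a reader might take from the text:

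- *Every patient who meets the severe definition faces a choice between no restart and two.* This holds only if the cross-reference is ignored.
- *Patients are lost to follow-up.* Section 13.1.1 itself asks for trial assessments to continue, and MRI and 6-weekly follow-up are kept.
- *The conflict leaves control patients on placebo alone.* That can follow any permanent cediranib stop under this protocol.
- *Step 5 would raise the dose of a patient already on 15 mg.* Section 7.4.1 bars any re-escalation.

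**Conclusion.** The inconsistency is real and should be fixed. Section 13.1.1 permanently stops both drugs for severe hypertension. The table it refers to stops cediranib temporarily, permits 20 mg and then 15 mg, and is silent on gefitinib/placebo. If Table 7 is assumed to govern timing, the unresolved part concerns patients who reach its permanent-stop step and whether they lose one drug or two. If 13.1.1 is read literally, the timing is in dispute as well, from the first severe event.

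The number of patients affected cannot be stated, because the protocol gives no expected rate of severe hypertension. The effect is on patient safety, exposure to both agents, and the timing of the discontinuation assessment and on-treatment visits. A reader might infer bias in the primary comparison. The documents do not support that: cediranib is given in both arms, and the PFS definition, the ITT population and the MRI schedule are the same whichever rule a site follows.

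**What to change.** Reword the 13.1.1 bullet to: *Hypertension meeting the permanent-stop step of Table 7 (severe step 8 or mild-moderate step 13)*. In those two steps, state that gefitinib/placebo is also stopped, in line with the 13.1.1 header. If the sponsor intends to stop cediranib only, move the bullet out of the both-drugs list instead.

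The main downside is that combination-arm patients who reach the permanent-stop step lose gefitinib that they might tolerate. The wording also brings mild-moderate step 13 explicitly under the both-drugs stop, whereas 13.1.1 currently names only severe hypertension, so the sponsor should confirm that this is wanted.

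The cost is one bullet and two short additions to Table 7, made through a protocol amendment with the approvals that section 17.4 requires and a note to sites. No extra patients or procedures are needed.

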### 13.1.2 Procedures for discontinuation from treatment

Patients who discontinue the trial treatment should always be asked about the reason(s) for their discontinuation and the presence of any adverse events. If possible, they should be seen and assessed by an investigator(s). The patient should return investigational products.

If all study treatment is stopped during the study, the Principal Investigator/Sub investigator will perform the best possible observation(s), test(s) and evaluation(s) as well as give appropriate treatment and all possible measures for the safety of the patient. In addition, they will record on the Case Report Form (CRF) the date of withdrawal, the reasons, and treatment at the time of withdrawal.

If only one study treatment is stopped during the study, the patient will continue with the trial assessments as before. Reasons for stopping the first drug must be recorded on the CRF. The discontinuation assessment is only to be carried out upon discontinuation of both trial drugs.

At withdrawal, all on-going SAEs must be followed until resolution, unless in the Investigator's opinion, the condition is unlikely to resolve due the patient's underlying disease.

All new AEs occurring for up to 30 days after the last dose of any study medication must be recorded in the CRF. Ongoing AEs thought to be caused by trial treatment will be followed up until resolution or death. All SAEs occurring up to 30 days after the last dose of any study medication must be followed until resolution.

Patients who are not receiving treatment, but are being followed up for tumour assessments should also be followed up for procedure related SAEs, these should be reported on an SAE report form (see [section 10.2.2](#) SAEs). AE collection beyond the 30 days post treatment is not required for patients who have progressed and are being followed up for survival only.

For patients who are withdrawn from study treatment for reasons other than disease progression every effort will be made to continue with collecting the trial MRI scans every 6 weeks. Follow up clinic assessments should be carried out every 6 weeks as detailed in [section 8](#).

If disease progression has been documented and the patient has withdrawn from study treatment, the long-term follow up information should be collected at least every 12 weeks by telephone contact with the patient, patient's family, or by contact with the patient's physician (see [section 8](#)). Please note that withdrawal from trial treatment is not compulsory for patients with disease progression, if the investigator feels that the patient is receiving benefit from trial treatment.

## 13.2 Withdrawal of Consent to Data Collection

If a patient explicitly states they do not wish to contribute further data to the trial their decision must be respected and recorded on the relevant CRF. In this event details should be recorded in the patient's hospital records, no further CRFs must be completed and no further data sent to UCL CTC.

## 13.3 Losses to follow-up

If a patient moves from the area, every effort should be made for the patient to be followed up at another participating trial site and for this new site to take over the responsibility for the patient, or for follow-up via GP. Details of participating trial sites can be obtained from the UCL CTC trial team

who must be informed of the transfer of care and follow up arrangements. The date of last contact should be documented when it is certain the patient is lost to follow up.

If a patient is lost to follow-up at a site every effort should be made to contact the patient's GP (if consented) to obtain information on the patient's status. Patients lost to follow up will be tracked by UCL CTC via the NHS Information Centre.

## **13.4 Withdrawal from Genetic Research**

A patient may withdraw consent from this genetic research at any time, independent of any decision concerning participation in other aspects of the main study described in this protocol. Voluntary discontinuation by the patient will not prejudice further treatment.

### **13.4.1 Procedures for discontinuation from genetic aspects of the study**

Patients who discontinue from the study should always be asked specifically whether they are withdrawing or continuing their consent for this genetic research. It must be established whether the patient:

- Agrees to the genetic sample and any DNA extracted from the sample being kept for genetic research in the future.
- Withdraws consent for the sample to be kept for genetic research in the future and wishes the sample to be destroyed. Destruction of the sample (or the DNA extracted from the sample) will only be possible so long as the particular sample is traceable. In the event that genetic research has already been performed, UCL CTC will retain the results and associated data for regulatory reasons but these will not be used in any subsequent analyses.

Depending on which samples the patient had originally consented to give, the above should be checked for the use of tissue biopsy samples, blood samples and / or post-mortem tumour samples.

The investigator is responsible for providing written notification to UCL CTC of any patient who has withdrawn consent for the use or future donation of any sample taken for genetic research, and specifying which particular samples. UCL CTC will provide written confirmation to the investigator of

the actions taken with the request (including details of sample destruction where relevant), which must be filed in the investigator study file.

---

## 14.0 Trial Closure

### 14.1 End of Trial

For regulatory purposes the end of the trial will be 6 months from the date the last patient finished trial treatment (the day after the date that the last trial drug was taken, i.e the first day that the patient is no longer taking either trial drug (not including treatment holidays of <14 days, or 21 days in consultation with the CI. If a patient has a treatment holiday which then is extended to withdrawal from the trial, the date of finishing trial treatment will be the first day of the treatment holiday)), or the date the last patient dies, whichever is sooner, at which point the 'declaration of end of trial' form will be submitted to participating regulatory authorities and ethical committees, as required.

If patients are alive following the end of trial, they will be followed up every 12 weeks for survival as per [section 8.1](#) (Schedule of assessments).

### 14.2 Archiving of Trial Documentation

At the end of the trial, UCL CTC will archive securely all centrally held trial related documentation for a minimum of 5 years. Arrangements for confidential destruction will then be made. It is the responsibility of Principal Investigators to ensure data and all essential documents relating to the trial held at site are retained for a minimum of 5 years after the end of the trial, in accordance with national legislation and for the maximum period of time permitted by the site.

Essential documents are those which enable both the conduct of the trial and the quality of the data produced to be evaluated and show whether the site complied with the principles of Good Clinical Practice and all applicable regulatory requirements.

UCL CTC will notify sites when trial documentation held at sites may be archived. All archived documents must continue to be available for inspection by appropriate authorities upon request.

### 14.3 Early discontinuation of trial

The trial may be stopped before completion as an Urgent Safety Measure on the recommendation of the ITSC or IDMC (see [section 12.5.2](#) ITSC and [section 12.5.3](#) IDMC). Sites will be informed in

writing by UCL CTC of reasons for early closure and the actions to be taken with regards the treatment and follow up of patients.

#### **14.4 Withdrawal from trial participation by a site**

Should a site choose to close to recruitment the PI must inform UCL CTC in writing. Follow up as per protocol must continue for all patients recruited into the trial at that site and other responsibilities continue as per CTSA.

## 15.0 Quality Assurance

All MRI scans used to produce the outcome data for the final analysis will undergo a retrospective central review at the end of the trial as per [section 7.7](#), before analysis. Local treatment decisions will be based on local imaging results.

## 16.0 Statistics

### 16.1 Sample size calculation

#### Statistical methods and determination of sample size

In the UK there is no standard second line treatment. Lomustine based treatments may be given but have a median PFS of only 2 months (8.32 weeks) (Yung et al. 2000). However, on the basis of the FDA approval for bevacizumab in GBM we suggest that the AVF3708g and NCI 06-C-0064E studies serve as the comparator for outcomes for this phase II study:

#### AVF3708g and NCI 06-C-0064E studies

The AVF3708g study was a phase II trial in 167 patients (85 treated with single-agent bevacizumab) with glioblastoma at first or second relapse (Friedman, 2010). Of note only the efficacy data from the bevacizumab monotherapy arm (n=85) was used to support FDA drug approval. Findings were supported by the Phase II trial of bevacizumab in 48 patients with relapsed glioblastoma (Study NCI 06-C-0064E) (Kriesl, 2009).

- AVF3708g study - objective response rate was 28.2 % (95% CI: 18.5 -40.3%)
- AVF3708g study - median response duration was 5.6 months (95% CI: 3.0-5.8 months)
- AVF3708g study - the 6-month progression-free survival (PFS6) rate was 42.6% (97.5% CI: 29.6-55.5%)
- AVF3708g study - the 6-month PFS rates for patients at first and second relapse were 46.4% and 27.8% respectively
- AVF3708g study – the median PFS in first and second relapse was 4.4 and 3.1 months respectively
- AVF3708g study - the median overall survival was 9.2 months (95% CI: 8.2-10.7 months), median overall survival at first and second relapse was 9.1 months and 9.2 months respectively
- Study NCI 06-C-0064E - response rate was 35% percent by Macdonald criteria (one CR, 16 PRs)
- Study NCI 06-C-0064E – median PFS of 16 weeks (95% CI: 12-26 weeks)

Assuming a median PFS of 4 months with cediranib (as equivalent to bevacizumab) and an expected median PFS of 6 months on the combination cediranib plus gefitinib arm a total of 112 patients are required to achieve 110 events in order to detect a hazard ratio of about 0.67 between the two arms. This assumes an accrual period of 18 months, maximum follow up of 36 months,  $\lambda_1 = 0.115$ ,  $\lambda_2 = 0.1733$ , and a one sided type I error of 10% with approximate power of 80%. The sample size was generated using Nquery Version 7.0.

